## Abstract

**Background:**

Increasingly, evidence-based health information, in particular evidence from systematic reviews, is being made available to lay audiences, in addition to health professionals. Research efforts have focused on different formats for the lay presentation of health information. However, there is a paucity of data on how patients integrate evidence-based health information with other factors such as their preferences for information and experiences with information-seeking. The aim of this project is to explore how people with multiple sclerosis (MS) integrate health information with their needs, experiences, preferences and values and how these factors can be incorporated into an online resource of evidence-based health information provision for people with MS and their families.

**Methods:**

This project is an Australian-Italian collaboration between researchers, MS societies and people with MS. Using a four-stage mixed methods design, a model will be developed for presenting evidence-based health information on the Internet for people with MS and their families. This evidence-based health information will draw upon systematic reviews of MS interventions from The Cochrane Library. Each stage of the project will build on the last. After conducting focus groups with people with MS and their family members (Stage 1), we will develop a model for summarising and presenting Cochrane MS reviews that is integrated with supporting information to aid understanding and decision making. This will be reviewed and finalised with people with MS, family members, health professionals and MS Society staff (Stage 2), before being uploaded to the Internet and evaluated (Stages 3 and 4).

**Discussion:**

This project aims to produce accessible and meaningful evidence-based health information about MS for use in the varied decision making and management situations people encounter in everyday life. It is expected that the findings will be relevant to broader efforts to provide evidence-based health information for patients and the general public. The international collaboration also permits exploration of cultural differences that could inform international practice.

## Background

### Evidence-based health information for patients

Systematic reviews represent the highest level of evidence of the effectiveness of health care interventions [1]. Historically, it has been clinicians who have used evidence from systematic reviews of controlled trials to stay abreast of current research and inform their practice [2]. Increasingly, however, evidence-based health information, including systematic reviews, is also being provided to lay audiences [3].

A recognised source of high quality evidence is the Cochrane Collaboration [4]. Cochrane systematic reviews summarise evidence from trials on the effects of treatments (medicines, surgery, rehabilitation), and behavioural and informational interventions. These reviews are the most rigorous summary of the evidence available. They are kept up-to-date, with new evidence added every few years [4]. In Australia, as in many parts of the world, Cochrane systematic reviews are available free to the public because of a nationally-funded subscription to The Cochrane Library [5]. In Italy, Italian translations of selected plain language summaries of Cochrane reviews are available free to the public on the PartecipaSalute web site [6] and in the "SM Italia" journal of the Associazione Italiana Sclerosi Multipla (AISM).

Research has shown that evidence-based health information may improve people's knowledge, capacity to manage their health, and their health literacy [7,8]. An overview of more than 50 systematic reviews demonstrated a range of positive effects that may stem from informing and educating people about their health, and involving them in the management of their health [7]. The authors concluded that informational interventions, in conjunction with professional advice, can improve people's health literacy: effects include improvement in health knowledge and recall, reduced anxiety, improved symptom management, and an increased sense of empowerment. Examples of interventions that were shown to improve patient health literacy include well-designed and written health information and educational support materials, computer-based and Internet-based information resources, and targeted mass-media approaches for specific population groups [7].

Research into accessible and usable formats for communicating evidence to lay audiences has flowed from these initiatives and has focused primarily on how to present evidence-based information clearly and unambiguously [9,10]. This is vital in order to avoid the non-transparent framing of risk and benefit information, and the associated consequences of unintended or intended manipulation of risk information [11,12]. The results of such studies are promising. For example, a randomised controlled trial of a drug leaflet advertisement that included a fact box about the medicine (quantifying outcomes with and without the drug) showed that the intervention improved patients' knowledge of drug benefits and side effects, resulted in better choices of drugs for symptoms, and improved patients' ability to make a realistic assessment of benefits, compared with a drug advertisement without the fact box [13].

### Health information and people with multiple sclerosis

Developments in the delivery of evidence-based health information have critical implications for providing information to people with multiple sclerosis (MS). Research has demonstrated that information plays an important role for people with MS to help them understand their diagnosis and treatments, and for self-management education [14,15]. MS is a complex inflammatory disease of the central nervous system, characterised by progressive neurological dysfunction, for which both a cure and the cause remain elusive. MS affects about 2.5 million individuals throughout the world [16]. Diagnosis typically occurs between the ages of 20 and 40. People with MS are high users of the full range of health services and, in particular, of medicines [17]. Despite the fears and anxieties that may arise from learning about the disease, the treatments, and self-management strategies, Wollin et al. [14] conclude that information is a critical component for informed decision making, problem solving, and self-determination.

The advent of disease-modifying drugs for MS means that people are actively seeking information about new treatments, and earlier attitudes of hopelessness are changing [18]. German research has found that people with MS were seeking more information than was provided at the time of their diagnosis, including information about potential treatments [18]. Later studies identified that people were requesting active roles with regard to medical decision making, and that they understood complex health and research information [19,20]. This finding opens up the possibility of shared decision making between patients and doctors about treatment options and health management.

Concurrently, the information-seeking landscape has changed dramatically with the addition of the Internet, which can facilitate greater opportunities for shared decision making. While medical professionals and MS societies have long been the preferred and trusted sources of health information, the Internet is gaining increasing prominence, particularly amongst younger people [21]. Studies conducted in Israel and the US found that between 64% and 82% of people with MS seek health information online [21,22].

In many countries, non-government organisations such as MS societies play a critical role in providing information for people with MS [23] and are using their web sites to provide information to people or to refer them to other high-quality sources. The move to online technologies reflects consumer demand and a population need to foster confident and skilled users of information. It is also fulfilling non-government organisations' roles to promote a higher level of client and community engagement in health care and service models, and to support policy for public participation in the health service system [24,25]. Users of non-government web sites are not only consumers. Health professionals play two important roles in people's Internet-based health-information seeking: 1) they may work in partnership with patients and patient groups to obtain and analyse information, and 2) they can guide Internet users toward reliable health information web sites [26]. The development of high quality, evidence-based health information on non-government sites must therefore accommodate these different user groups and their needs.

### Making evidence meaningful for people

Our assertion is two-fold. First, that people with MS who read summaries of systematic reviews for health information may need additional documented support or advice to help them understand how the information can be applied to their personal context [14,27]. This documentation may also support people to use the information in the systematic reviews when making decisions and judgements with their doctors about treatment preferences or self-management options that will work for them. There is a paucity of data about the experiences people have when needing to assess evidence-based information and integrate it into their own context and value system. The second part of our assertion addresses the process of developing complex interventions, such as health information services for patients. In order to supply a service that is applicable to a population group, the information and other needs of those individuals must first be understood. The next steps are to identify the evidence base, build or refine the theoretical concepts, then evaluate the processes and outcomes for implementation, before trialling the intervention [28].

We know that many patients and family members want to understand the evidence that supports treatment options [10]. They also want to know how the research relates to them individually [29], as well as the implications of the findings for their future treatment choices and management options. This creates a challenge for services that provide health information based on research because that information may not be sufficient for an individual to make the connection between the research and their own circumstances. Further information may need to be provided by the health information service in order for people to be able to make judgements about the appropriateness of a treatment for their own context. Furthermore, as new research is conducted, people may need to understand how new information relates to what they already know. For example, they may need to decide if a new treatment would be substantially better for them, maybe with reduced risks or adverse effects, compared with their current options.

The aim of this project is 1) to explore how people with MS assess and integrate health information into their lives according to their needs, experiences, preferences, and values, and 2) how documentation to support people to make the connection between health information and their needs, experiences, preferences and values can be provided in an online resource of evidence-based health information for people with MS, and their families.

## Methods

This project will employ a mixed methods approach involving four stages: qualitative research (Stage 1); action research (Stage 2); operational research (Stage 3); and evaluation (Stage 4) (see Figure 1). A mixed methods study combines and builds knowledge derived from qualitative and quantitative research methods [30]. It aims to generate theory and test it in latter stages.

**Figure 1 F1:**
[figure not shown]
**Flow chart of IN-DEEP project**.

The IN-DEEP project (Integrating and deriving evidence, experiences and preferences: Developing evidence-based health information applicable to decision making and self-management by people with MS) is a collaboration of project teams in Melbourne, Australia (led by SH) and Milan, Italy (led by GF). It will be conducted in parallel in Australia and Italy. The studies will be conducted as stand-alone projects but will follow the same stages and mixed methods approach. We anticipate some methodological differences between the projects as we progress due to differing findings from early research stages and contextual differences between countries. A comparison of similarities and differences in project findings between Australia and Italy will be considered at each stage and will be reported.

### Advisory groups

Prior to the commencement of the research, an Italian and an Australian advisory group will be formed. The advisory groups at each site will play key roles in guiding all project stages and will include members of the local research teams, local MS society staff (MS Australia in Australia and AISM in Italy), and people with MS. Academic-community partnerships benefit from the different perspectives and organisational styles [31]. Additionally, there is strong evidence that involving patients in the development of health information leads to information that is more understandable [32].

### Participants

#### People with MS, and family members of people with MS

People with MS, and family members (partners, parents, children and siblings aged over 18) of people with MS will be included in the study. It is often the case that close family members may be as or more actively involved in finding and assessing health information as the person with MS. To reflect the gender and age distribution of people with MS, we will aim to include women with MS in an approximate 3:1 ratio to men, and include participants in the age range of 20-69 [17]. Individuals outside that range (over 18 years) if they are interested to participate will also be accepted. A mix of people newly diagnosed with MS (up to three years since diagnosis), those with later stages of MS (living with MS for at least 4 years), and people taking immunotherapy medications will also be sought in order to capture a broad range of experiences. People with MS and family members of people with MS will be invited to take part in all four stages of the research.

#### MS society staff and health professionals

As well as including people with MS and their family members, Stages 2 and 3 will also include clinicians involved with MS treatment, and MS society staff who work in a health information capacity. The involvement of participants from a variety of perspectives means that the research can gain insight into a range of potential barriers to uptake of information from an online resource, and then be able to take steps to reduce these barriers in practice.

### Participant sampling

Purposive sampling will be used both in Australia and Italy. People with MS, family members, and health professionals will be recruited using the communication channels of MS Australia in Australia, and AISM in Italy and their networks of related organisations. In Australia, snowball sampling from the pool of people with MS and family members will also be undertaken, while in Italy collaborating neurologists will identify eligible patients with MS and family members. From these pools of participants, selected participants will be invited to take part in focus groups and the successive stages of the study.

### Research activities

#### Stage 1: Qualitative research

The aim of Stage 1 is to document and analyse the needs, experiences, preferences, and values of people with MS when assessing and integrating evidence-based health information into their decision-making about, and management of, their health. Between four and six focus groups will be conducted in each country. In Australia, focus groups will be held in Victoria and Tasmania, with at least one in a non-metropolitan area. In Italy, focus groups will be conducted in Northern, Central and Southern Italy. Where possible, groups will be stratified according to length of time since diagnosis and whether or not participants are a person with MS or a family member. The focus groups will last approximately one hour and will be conducted by two experienced researchers. The focus groups will be audio-recorded and transcribed verbatim.

Focus group topics will be based on four main questions: (1) Where do you get reliable information about the evidence of the effectiveness of treatments for MS?; (2) What kinds of information do you need, and how do these needs change over time?; (3) How do you use the Internet to access information about treatments for MS?; and (4) How do you assess the quality and usefulness of this information?

The focus group transcripts will be analysed by thematic analysis. Two researchers will independently read the transcripts multiple times and identify emerging themes. Agreed codes will be used to categorise the themes.

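### None of the four listed Stage 1 main questions directly asks how people integrate evidence with their own values and situation when making a decision

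*Protocol article*

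**What the plan says.** The project's first aim, at the end of the Background (Making evidence meaningful for people), is "to explore how people with MS assess and integrate health information into their lives according to their needs, experiences, preferences, and values". The same section gives the reason: "There is a paucity of data about the experiences people have when needing to assess evidence-based information and integrate it", where the missing link is to the person's own context and value system.

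The Stage 1 section repeats the aim for the focus groups. Their purpose is to record and examine "needs, experiences, preferences, and values of people with MS when assessing and integrating evidence-based health information into their decision-making", and the sentence goes on to include management of health.

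The instrument follows in the same section: "Focus group topics will be based on four main questions". In paraphrase, except for the second, the questions are:

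1. From which sources participants obtain trustworthy evidence that MS treatments work.
2. "What kinds of information do you need, and how do these needs change over time"
3. In what way participants go online to find treatment information.
4. By what means participants judge whether that information is good and useful.

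There are four to six groups per country, each of about an hour and run by two experienced researchers. Transcripts are analysed thematically for emerging themes. The Stage 2 section says that the supporting documentation for personal decision making will be shaped by Stage 1 themes. The Stage 4 section says that the resource will be judged against what Stage 1 gathered.

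**The concern.** The aim has two verbs, assess and integrate. The listed questions follow the first and do not name the second. A participant could answer all four fully and never describe a decision, how a finding was applied to their own case, or what they valued in making a choice.

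Integration is the part on which the protocol says data are scarce, and it is in the project's title. If Stage 1 yields little on it, the Stage 2 team drafts decision-support material with thin data on how people decide. Stage 4 would then compare the resource with a benchmark made up mostly of information-seeking needs. The resource could look satisfactory without having been tested on the project's distinctive purpose. The planned comparison between Australia and Italy would also suffer if the topic surfaced in some groups and not in others.

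**Working it through.** No calculation applies. The check sets each element of the first project aim and of the Stage 1 aim beside the four main questions.

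- **Needs:** covered. Question 2 asks about them directly, including change over time.
- **Assessing information:** covered. Question 4 asks about it directly.
- **Experiences:** partly covered. Questions 1 and 3 elicit experience of looking for information, not of using it.
- **Preferences:** indirect at most. Questions 1 to 3 may reveal preferred sources and kinds of information, but none asks about preferences between treatment or management options.
- **Values:** no question.
- **Integration into decisions or into managing one's health:** no question. Question 4 comes closest, since useful information is presumably information one can apply. But it asks people to appraise the information, not to say how they weighed it in a choice.

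The count of main questions that directly elicit integration, values or a decision is therefore 0 of 4.

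Two further observations bear on the remedy. Questions 1 and 3 overlap in part: both concern finding information and both refer to treatments for MS. They are not duplicates, because question 3 is about the medium in which the product will be delivered. Question 2 is not confined to treatments, so information needs for self-management can be raised there.

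The dependence of later stages can be read from the text. Stage 2 has other inputs: methods from the literature, two review panels per country, and advisory groups that include people with MS. The panels discuss formats and fine-tune the summaries and supporting documents. They can correct that material, but they are not set up to replace the Stage 1 enquiry into how people decide. Stage 4 takes its criterion from Stage 1, although it also determines separately whether people plan to use the information in health decisions.

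**The case against.** The strongest reply is that these are described only as main questions on which topics will be based. A moderator's guide with probes may exist, and a journal article commonly leaves it out. The discussion is open, the moderators are experienced and the analysis looks for emerging themes, so integration can surface without its own question. Asking people living with MS what makes information useful, or how their needs have changed, invites talk of personal circumstances. All of this stands, and it limits the point.

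It does not remove it. The point is not that a guide is missing. The article states its main questions, and they do not match the aim stated in the same section. Sources and Internet access each have a main question, while the construct that defines the project would have to rely on probes that are not shown. Thematic analysis can find only what was said.

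A reader might infer that Stage 1 fails to collect the data for the first aim. The documents do not support that: needs and assessment are asked about directly, experiences in part, and integration may still emerge. A reader might also divide the hour among questions and participants to show that time is too short. The article gives no group size, and the result would not change if the number of questions stayed at four, so that argument carries no weight. Nor does the protocol support saying that the model rests on information-seeking data alone, given the other inputs to Stage 2.

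**Conclusion.** The point holds as a mismatch between aim and instrument. The four listed main questions address sources, needs, Internet access and appraisal. None directly elicits the integration, values and decision-making component of the first project aim and of the Stage 1 aim. Its size is 0 of 4 questions on that component, with the rest of the aim covered wholly or in part.

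The likely effect is thin and uneven data on integration, not its absence. How thin cannot be judged from the article. The conclusion assumes that the main questions largely structure each session and that no unseen probe already gives integration a fixed place. If such a probe exists and is used in every group, little of the concern remains. The point is worth acting on because the change is small, two later stages draw on Stage 1, and what is not elicited in the groups cannot be recovered in analysis.

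**What to change.** Before the first focus group, add one main question in both countries. For example: Think of a recent decision about treating or managing MS. How did you weigh the information you had against your own situation, preferences and values, and what was missing? If the topic guide already holds such a probe, raise it to a main question so that every group is asked it and the two countries can be compared.

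Make room by shortening or combining questions 1 and 3, for instance by asking where and how, including on the Internet, people find information about treating and managing MS. Keep an explicit prompt on Internet use, because the product is an online resource.

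The number of groups and the session length need not change. The cost is an edit to the topic guide and slightly less time on information sources and Internet use.
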